### Methods for additional analyses (e.g., subgroup analyses)

Analyses will be performed in the birthweight less than 1000 g and birthweight of 1000 g or more subgroups to assess the homogeneity of the difference between the two treatment groups. These subgroup analyses will be supplemented by interaction tests between the treatment and the subgroup variables. The results will be graphically presented using Forest plots.

### Methods in analysis to handle protocol non‐adherence and any statistical methods to handle missing data

Patients with missing outcome data will be censored at last contact. Descriptive statistics on the use of non-protocolized modes as well as intolerance of conventional ventilation mode (duration in days and percentage of time in study spent on HFOV) will be provided.

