### Primary outcome

Death or BPD at 36 weeks’ postmenstrual age will be used as the primary outcome. BPD will be diagnosed by clinical physicians. The definition and diagnostic criteria of BPD is according to NIH 2018 [16]. We have chosen “death or BPD (36w)” as our primary outcome to maintain similarity with previous trial comparing VTV and PCV [10].

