## Data collection and management

### Data collection

Data will be collected on a web-based electronic case record form by research investigators. Some collected data can be obtained from the clinical records, and the rest will be collected from the ventilator at the bedside. Clinical information will be collected in three forms at the following times: demographic information will be collected at trial entry, baseline information will be collected after randomization, and outcome information: including primary outcomes, secondary outcomes, and others. Outcomes will be collected before discharge. And other observational information like ABG, ventilator settings, and respiratory mechanics will be collected 1 h after using the ventilator and same time each day until extubation.

Any participants who discontinue or deviated from the intervention protocol has to collect the specific reason.

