### Statistical methods

All efficacy analysis will be conducted on an intention-to-treat basis. The SPSS version 26.0 (SPSS, Chicago, IL) software will be used for statistical analysis. Clinical characteristics of infants will be described as mean with standard deviation or median with range for continuous variables and rate or percentage for categorical variables. Absolute risk differences with 95% confidence intervals (CIs) between VTV and PCV will be calculated for binary outcomes, and odds ratios with 95% CIs will be estimated by univariate logistic regression, followed by multivariate logistic regression if the prespecified baseline characteristics are unbalanced between the two groups. Absolute mean differences with 95% CIs (using *t*-test) or mean differences with P25-P75 (using Hodges-Lehmann) will be also calculated for continuous outcomes, and adjusted differences will be estimated by multivariate liner regression if needed. A *P* value < 0.05 was considered statistically significant.

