## Trials status

Version number: 3, 2023 March 01.

This trial started recruiting patient since 2023 May 01. Sixty-eight infants will be recruited over 1 year. The trial will terminate when the last recruited infant is discharged from the hospital or dies.

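### The rule to censor missing outcomes at last contact cannot be applied to a yes/no primary outcome at 36 weeks' postmenstrual age

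*Protocol article*

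**What the plan says.** The section of the Protocol article on non-adherence and missing data states: "Patients with missing outcome data will be censored at last contact". It gives no other rule for missing outcomes.

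The section Primary outcome defines the endpoint as death or BPD at 36 weeks' PMA, a status at a fixed time. Under Statistical methods, absolute risk differences "between VTV and PCV will be calculated for binary outcomes", and "odds ratios with 95% CIs will be estimated by univariate logistic regression". Mean or Hodges-Lehmann differences "will be also calculated for continuous outcomes". The same section says: "All efficacy analysis will be conducted on an intention-to-treat basis". The article names no Kaplan-Meier, log-rank, Cox or other time-to-event method.

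Three other places bear on which outcomes could be missing:

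- Data collection: "Outcomes will be collected before discharge".
- Trials status: "The trial will terminate when the last recruited infant is discharged from the hospital or dies".
- Definitions: the term withdrawal covers both infants who die of non-respiratory causes and infants discharged early, including at the family's wish.

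**The concern.** Censoring belongs to survival analysis, where a participant contributes time at risk up to the last contact. A risk difference or a logistic regression needs a yes or a no for each infant and has no place for a censored one. The duration outcomes do not rescue the sentence, because they too are compared by t-test, Hodges-Lehmann or linear regression.

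Without imputation, whoever runs the analysis must turn a censored infant into one of two things:

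- **Excluded.** This departs from the intention-to-treat statement.
- **Counted as free of death and BPD.** This lowers the event rate in each arm and, if missingness differs by arm, biases the comparison.

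The protocol does not choose between them, so the choice could be made after the data are seen.

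Two features elsewhere add to the risk. A non-respiratory death before 36 weeks is a primary event, but Definitions labels it a withdrawal, and it could be lost if withdrawn infants are handled as missing. An infant discharged before 36 weeks may also have no 36-week status, since outcomes are to be collected before discharge and no later ascertainment of the primary outcome is described.

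**Working it through.** **Inputs.** From Sample size: 26% (VTV) and 64% (PCV), 31 per group for 90% power at two-sided 0.05, and 68 infants in total. With 1:1 allocation this is 34 per arm. The number of missing outcomes is not given, so two values are assumed:

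- 3 per arm, which leaves the 31 per group that the calculation asks for.
- 7 per arm, since 20% of 34 is 6.8. The 20% is the protocol's withdrawal allowance, borrowed here as a high case.

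**The plan's own figure.** With unpooled variance, n = (1.960 + 1.282)² × (0.26 × 0.74 + 0.64 × 0.36) / 0.38² = 30.8, so 31 per group reproduces. The point below does not depend on it.

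**Risk difference under each reading.** Let m be the number missing per arm. Expected observed events are E = rate × (34 - m). For VTV minus PCV:

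- dropped: the difference in observed rates, if missingness is unrelated to outcome
- event-free: (E_VTV - E_PCV) / 34
- best for VTV: (E_VTV - E_PCV - m) / 34
- worst for VTV: (E_VTV + m - E_PCV) / 34

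| Observed rates | m | E_VTV, E_PCV | Dropped | Event-free | Best | Worst |
|---|---|---|---|---|---|---|
| 26% vs 64% (design) | 3 | 8.06, 19.84 | -38.0 | -34.6 | -43.5 | -25.8 |
| 26% vs 64% (design) | 7 | 7.02, 17.28 | -38.0 | -30.2 | -50.8 | -9.6 |
| 40% vs 60% (assumed) | 3 | 12.40, 18.60 | -20.0 | -18.2 | -27.1 | -9.4 |
| 40% vs 60% (assumed) | 7 | 10.80, 16.20 | -20.0 | -15.9 | -36.5 | +4.7 |

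Entries are percentage points. For example, at the design rates with m = 7, event-free coding gives (7.02 - 17.28)/34 = -0.302, and the worst case gives (14.02 - 17.28)/34 = -0.096.

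**Power.** These figures use the pooled normal approximation, 34 per arm, the design rates, and equal missingness unrelated to outcome. Power is 90.1% with nothing missing. At 20% missing it is 82.3% if infants are dropped (27.2 per arm) and 75.4% if they are counted event-free (20.8% vs 51.2%).

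**Unequal missingness.** Assume a true rate of 45% in both arms, with 10% missing in one and 30% in the other. Event-free coding then gives 0.45 × 0.90 - 0.45 × 0.70 = 0.405 - 0.315, a spurious difference of 9 points.

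**The case against.** The strongest reply is that the word censored is loose wording for exclusion. If missingness is unrelated to outcome, a complete-case risk difference is unbiased and costs only precision: still 38 points, with about 82% power even at 20% missing. The event-free reading is nowhere stated. This is fair as far as it goes. But exclusion still conflicts with the intention-to-treat statement, and nothing in the protocol supports missingness unrelated to outcome.

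Several stronger readings are tempting, and the documents do not support them:

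- **That the plan expects 20% of outcomes to be missing.** The 20% in Sample size is withdrawal, which Definitions takes to include deaths. Those infants have a known status.
- **That the rule can by itself decide the trial's answer.** At the design rates the bounds stay below zero even with 7 missing per arm. A change of sign needs that loss and a smaller effect together, and both are assumptions.
- **That outcomes are collected only up to discharge, so every infant discharged before 36 weeks lacks the primary outcome.** The text says before discharge, while the definition of loss to follow-up and the phrase about last contact hint at later contact. The text is ambiguous.
- **That early discharge tracks prognosis.** This is plausible, but the documents give neither a mechanism nor a figure.

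The remedy is also not free. Under Confidentiality, contact details are kept for a possible later follow-up study, not for ascertaining this outcome. Primary outcome says "will be used as the primary outcome. BPD will be diagnosed by clinical physicians", so a telephone call alone may not settle every case.

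**Conclusion.** The concern holds in a limited form. The censoring sentence is a rule that the protocol fixes, not a detail left to an analysis plan, and it fits none of the planned analyses. An analysis plan that followed it would inherit the ambiguity.

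Its size depends on a missing rate that the protocol does not give. Over the assumed range of 3 to 7 missing per arm at the design rates, the gap between best and worst case is about 18 points (-43.5 to -25.8) to 41 points (-50.8 to -9.6). Event-free coding takes 3 to 8 points off a true difference of 38. The direction of effect is safe throughout that range at the design rates, and also at 40% vs 60% with 3 missing per arm. It is not safe at 40% vs 60% with 7 missing.

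The labelling of non-respiratory deaths as withdrawals is a risk, not a demonstrated loss of events: the protocol does not say that withdrawn infants will be treated as missing.

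**What to change.** 1. Delete the censoring sentence.
2. State that every death before 36 weeks' PMA counts as a primary event, whatever its cause and whether or not the infant is labelled a withdrawal.
3. For infants discharged earlier, obtain vital status and respiratory support at 36 weeks' PMA by record check or telephone, with consent extended to this purpose.
4. For outcomes still missing, name a method suited to a binary outcome. Multiple imputation using arm, birthweight stratum and gestational age is one option among several; the detailed model can sit in the analysis plan.
5. Report best-case and worst-case bounds as a sensitivity analysis.

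The cost is a formal amendment with ethics review, as the section Protocol amendments requires for a change in analyses, plus some follow-up contacts and a little extra analysis. Recruitment had already begun in May 2023, so infants enrolled before the amendment would need consent for the added contact. No change in sample size is needed for this point.

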### Sample size

An RCT of VLBW infants with respiratory distress syndrome(RDS) receiving VTV or PCV as their primary respiratory support mode showed that the BPD/death rate of 26% and 64% respectively [15]. Based on this study, a sample size of 31 in each group will have 90% power to detect statistically difference at a 0.05 tow-sided significance level (MedSci, Shanghai, China). Considering a 20% of patients may withdraw from the research, a sample size of 68 will be appropriate.

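### Censoring at last contact cannot be applied to a yes/no outcome at 36 weeks when no time-to-event analysis is planned, so the rule for missing outcomes needs rewriting

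*Protocol article*

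**What the plan says.** The protocol article's section on non-adherence and missing data gives one rule for missing outcomes: "Patients with missing outcome data will be censored at last contact".

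The other relevant statements are:

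- **Primary outcome:** death or BPD at 36 weeks' "postmenstrual age will be used as the primary outcome". This is a binary status at a fixed time.
- **Statistical methods, population:** "All efficacy analysis will be conducted on an intention-to-treat basis".
- **Statistical methods, binary outcomes:** "Absolute risk differences with 95% confidence intervals (CIs) between VTV and PCV will be calculated for binary outcomes". The relative measure comes from a regression model: "odds ratios with 95% CIs will be estimated by univariate logistic regression".
- **Statistical methods, continuous outcomes:** a t-test, or "mean differences with P25-P75 (using Hodges-Lehmann) will be also calculated for continuous outcomes", with linear regression for adjustment.
- **Sample size:** "Considering a 20% of patients may withdraw from the research", with 68 infants in total.
- **Definitions:** withdrawal covers both death and early discharge from non-respiratory causes, and family wishes are among the listed reasons.
- **Data collection:** outcomes are gathered before discharge.

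**The concern.** Censoring has a meaning only where the analysis uses follow-up time. No Kaplan-Meier, log-rank or Cox analysis appears in the article, so the stated rule has nothing to act on. Whoever runs the analysis must replace it with something else, and the wording does not say what. That choice could then be made after the data have been seen, in a trial of 68 infants where a few reclassified infants can move the result.

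Missing 36-week status is foreseeable. An infant taken home early, before 36 weeks, may have no BPD assessment. The definition of withdrawal adds a second problem. A non-respiratory death before 36 weeks is a known primary event, yet it is also labelled a withdrawal, and nothing in the text prevents it from being treated as missing and censored.

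**Working it through.** **1. Rule against methods.**

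| Outcome type | Listed method | Can it use a censoring time? |
|---|---|---|
| Binary, including the primary | Risk difference, logistic regression | No |
| Continuous, including lengths of ventilation, oxygen use and stay | t-test, Hodges-Lehmann, linear regression | No |

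Two practical substitutes remain closest to the wording:

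- *Drop the infant.* This is a complete-case analysis, and not all randomised infants are then analysed.
- *Carry the status at last contact.* BPD status is set at 36 weeks, so an infant last seen alive before then is event-free by construction. A duration cut at last contact would enter the t-test as if it were complete.

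**2. The plan's own sample size.** The Sample size section gives a "BPD/death rate of 26% and 64% respectively" for VTV and PCV, 90% power and two-sided 0.05. With the unpooled formula:

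n = (1.960 + 1.282)² × (0.26×0.74 + 0.64×0.36) / 0.38² = 10.51 × 0.4228 / 0.1444 = 30.77, rounded up to 31 per arm.

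This matches the stated figure.

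**3. Cost in power of each substitute.** Inputs are 34 per arm (68/2) and rates of 26% and 64%. Missingness is assumed equal in the arms and unrelated to outcome. The number missing is not given in the document. I use 3 to 7 per arm (9% to 21%), where 7 is roughly the planned 20% withdrawal (0.20 × 34 = 6.8).

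Scored event-free with m missing, each rate is multiplied by (34 − m)/34:

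- m = 3: 0.26 × 31/34 = 23.7% and 0.64 × 31/34 = 58.4%, a difference of 34.6 points.
- m = 7: 0.26 × 27/34 = 20.6% and 0.64 × 27/34 = 50.8%, a difference of 30.2 points instead of 38.

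If the infants are dropped, the expected difference stays at 38 points and 34 − m per arm are analysed.

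Power of the two-sided 5% Wald test from logistic regression is found by enumerating all possible tables. Tables with an empty cell count as not significant.

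| Missing per arm | Scored event-free | Dropped |
|---|---|---|
| 0 | 88.7% | 88.7% |
| 3 | 84.6% | 88.0% |
| 7 | 77.7% | 79.7% |

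**4. Type I error with no true effect.** The test is the same, with a common true rate of 45% or 64% in both arms.

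| Missing, one arm vs the other | Event-free (45% / 64%) | Dropped (45% / 64%) |
|---|---|---|
| 0 vs 0 | 4.3% / 5.0% | 4.3% / 5.0% |
| 7 vs 7 | 3.5% / 1.6% | 4.0% / 4.2% |
| 9 vs 5 | 5.7% / 4.8% | 4.7% / 4.8% |
| 7 vs 2 | 7.1% / 8.5% | 4.8% / 4.6% |

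At 7 versus 2 scored event-free, the false difference is 0.45 × 5/34 = 6.6 points to 0.64 × 5/34 = 9.4 points. Inflation therefore needs both event-free scoring and losses that clearly differ by arm.

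**The case against.** **The protocol never says missing infants are scored event-free.** This is correct. The Sample size section inflates for withdrawal, which fits leaving infants out at least as well. If they are dropped at random, type I error stays near nominal and only power is lost. A reader might infer that the rule as written inflates the false-positive rate. The documents do not support that: it takes a reading they do not state, together with an imbalance in losses they do not predict. Larger inflation can be produced by assuming a more extreme split, but nothing in the text points to one. Clinicians know the arm, but families are blinded, which weakens the case for strongly arm-related loss without excluding it.

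**Twenty per cent withdrawal is not twenty per cent missing outcome.** This stands. Withdrawals include deaths whose status is known, outcomes are collected before discharge, and the trial runs until the last infant is discharged or dies. Seven missing per arm is therefore near the top of the plausible range.

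**Best-case to worst-case bounds.** A reader might cite their width against the censoring rule. Those bounds depend on how many infants are missing and are the same under any rule, so they do not count against this sentence.

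**Dropping infants contradicts intention-to-treat.** This is too strong. Analysing observed infants in their assigned arm is an incomplete intention-to-treat analysis, not a flat contradiction of it.

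**The detail may be in an analysis plan that is not shown.** An imputation model could well be. But the protocol does not stay silent here: it fixes a rule, and an analysis plan could make the primary analysis work only by departing from it.

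**Conclusion.** The point holds as a fault in a stated rule: censoring at last contact cannot be carried out with the binary primary outcome and the analyses listed. That conclusion rests on the text alone and needs no assumption about how many outcomes will be missing. The overlap between the withdrawal definition and the primary outcome must be reconciled at the same time.

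The size is moderate. With 3 to 7 missing per arm, equal in the arms and unrelated to outcome, power drops from 89% to 85–78% under event-free scoring and to 88–80% under dropping. Under event-free scoring the 38-point difference shrinks to 30 points at the upper end. Missingness related to outcome was not modelled. The grade is should-fix: the error is plain and cheap to correct, but the documents do not show that it would by itself decide the trial's result.

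**What to change.** - Delete the censoring sentence for the binary outcomes.
- State that all randomised infants are in the primary analysis in their assigned arm.
- State that every known death by 36 weeks is a primary event, including deaths classed as withdrawals, and align the Definitions section with this.
- State that an unknown 36-week status is not scored as event-free.
- Prespecify a method for unknown status. Multiple imputation with a small model (arm, birthweight, gestational age) is one option, and all three variables are already available. A richer model, or separate models by arm, would be unstable with about 27 observed infants per arm. The last respiratory support level is not a safe predictor, because no dated post-extubation level is listed among the collected data.
- Add a best-case/worst-case or tipping-point sensitivity analysis, and report the number missing by arm.
- If censoring is kept for durations, pair it with a time-to-event method that treats death as a competing event.

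The cost is a protocol amendment, which the protocol already requires for changes to analyses, a little extra analysis and slightly wider intervals. No extra infants are needed. The change should be made before outcomes are examined by arm.

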### Composition of the data monitoring committee, its role and reporting structure

A DSMB will ensure patient data safety during the study and oversee the overall conduct of the trial. The DSMB consisting of two study members who are independent from funder or sponsor, who both have no competing interests to declare, will be responsible for the preservation of data as well as the verification of data authenticity and correctness to ensure the accuracy of study results.

After 10 patients are included, the DSMB will assess the occurrence of adverse events in relation to the study’s relevance and discuss with the study team whether the intervention needs to be modified.

### Harms

Although we do not anticipate any additional risks associated with study participation, the following monitoring methods will be used to ensure patient safety. All serious or unexpected adverse events that are potentially causally related to the intervention, or are considered potentially directly related to study participation (i.e., unlikely to occur if the patient does not participate in the study), will be reported to the CC and monitor via an electronic case report form and reviewed by the DSMB at the meeting. Serious adverse events (SAE) should be documented in the source and SAE. Investigators should promptly report SAEs that are potentially or clearly relevant to the study intervention within 24 h of learning of the event and update additional information as it becomes available. Each site is also required to report SAEs that are potentially or clearly related to the study intervention to the ethic board.

### Auditing

The research project members will meet weekly throughout the study to report the implementation of the study. ESC will meet when accrued 10 patients to review trial conduct. Source data verification will be performed on a selection of the patients by comparing the data in patient’s record with the data collected. For selected participants, the presence of signed informed consent and compliance with inclusion and exclusion criteria will be checked.

### Protocol amendments

If there are any modifications in the protocol during the study, including changes to study design, eligibility criteria, outcomes, analyses, patient population, sample sizes, study procedures, a formal amendment to the protocol is required and submitted to the ethics committee for review.

### Dissemination plans

The results of the study will be published in peer-reviewed journals and presented at national and international conferences. Communication, reporting, and publication of the study results will be the responsibility of the study’s principal investigator and steering committee.

## Discussion

A follow-up study of VLBW infants (*n* = 270) who had been treated with VTV or PLV after birth found that, in the short term, VTV reduced the incidence of interstitial lung disease during hospitalization, length of hospital stay, and mortality rates. Long-term follow-up found fewer deaths or neurological injuries in the VTV group compared with PLV [17]. A meta-analysis found that for ELBW infants (*n* = 247), there were no statistically significant differences between VTV and PLV in the mortality, BPD, length of MV, hypocapnia, FiO_2_, IVH/ PVL, and air leak syndrome. The use of VTV did not increase in adverse events, suggesting that the use of VTV in ELBW is safe [13]. However, evidence is lacking regarding the benefits of VTV in VLBW. It is important to provide an RCT to help better understand this mode in VLBW. We carefully designed this single-center RCT. We chose BPD or death at 36 weeks’ postmenstrual age as our primary outcome. In addition to that, we will also collect ventilator adjustments, lung mechanics, and other secondary outcomes. The study will pay special attention to ventilator-associated lung injury. We hope this trial to add a significant contribution regarding the benefits of VTV for VLBW patients.

In conclusion, we describe a protocol for a single-center RCT in VLBW patients to compare two ventilator modes, VTV and PLV.

